### Organization and conduct

This trial is approved by the Regional Ethics Committee (REK South-East D, ref. nr: 522416) and the Data Protection Officer at Oslo University Hospital (ref.nr: 22/22307). Sensitive data will be stored in a de-identified format on a secure data server at Oslo University Hospital. The linkage file will be stored in a separate software (Medinsight; Oslo University Hospital, Oslo, Norway). Data as “minimal data sets” will be available as Supporting Information upon publication of the original article. To ensure confidentiality, these data will not include demographic details. Further access to data may be granted upon reasonable request and approval by the Data Protection Officer.

## Discussion

In this present study, we will combine two established experimental interventions: LBNP and thigh cuff inflation. We thereby aim to explore whether this combination can serve as a model in awake humans to elucidate the systemic and cerebral hemodynamic effects observed with zone 3 REBOA in hemorrhage.

The hemodynamic response to REBOA in non-cardiac arrest settings has primarily been described in animal models. In a normovolemic canine model, ligation of the descending aorta led to increased systolic blood pressure and end-systolic and end-diastolic volumes of the left ventricle. Simultaneously, flow in the superior vena cava increased, indicating an increased flow to this vascular bed [26]

In a porcine model of hemorrhagic shock, REBOA increased proximal pressure, carotid artery blood flow, and brain oxygenation [27]. The combined effects of TBI and REBOA were studied in a rodent model. The setup and results were quite complex, but REBOA increased MAP and cerebral blood flow in the group with sham-TBI [28]. Although one pig model of TBI and hemorrhage did not find increased TBI-progression [29], the question of possible adverse effects of supranormal precerebral arterial pressures has been raised.

In a registry study, systolic blood pressure >160 mmHg was associated with worse outcomes in TBI-patients [30], and a case report described fatal intracerebral hemorrhage in a patient treated with REBOA for a pelvic hemorrhage who had a concomitant TBI [31]. However, the effects on MAP were less for zone 3 REBOA compared to zone 1 in a pig model with hemorrhage [32]. Therefore, conducting a study on the systemic and cerebral hemodynamic effects of hemorrhage and increased afterload in awake humans seems justified.

### Methodological considerations

To our knowledge, this is the first attempt to establish an experimental model of REBOA by combining LBNP and thigh cuffs. Accordingly, we have chosen to focus primarily on the main hemodynamic parameters. Depending on the results of the current study, future studies may incorporate laboratory analyses, such as arterial blood gas and lactate measurements, to further improve the model.

To the best of our knowledge, only one previous study has combined LBNP with arterial occlusion at thigh level [18]. However, in that study, lower limb tourniquets were applied before exposure to LBNP, potentially limiting the redistribution of blood to the lower limbs below the tourniquets. In contrast to REBOA, which only occludes the arteries, our model, similar to the tourniquet model, also occludes the veins. As venous congestion is already present in the lower extremities with LBNP, the consequences of additional venous occlusion due to thigh cuff inflation may be insignificant. This question remains to be elucidated.

Thigh cuff inflation will only occlude the vascular beds distal to the femoral arteries, thereby missing the pelvis in comparison to a zone 3 REBOA. One may consider occluding additional vascular beds, for example, by manually compressing the abdominal aorta against the columna. However, at this point, we do not wish to impose excessive hemodynamic interventions due to a lack of experience in combining these two interventions, as each in isolation includes quite profound hemodynamic effects.

While LBNP is generally not very uncomfortable, the application of thigh cuff inflation may cause pain, triggering the sympathetic nervous system and elevating the arterial blood pressure [25]. This may confound the hemodynamic effects of vascular occlusion. However, since both arterial occlusion and increased sympathetic activity tend to increase blood pressure, pain will not counteract the intended effect of vascular occlusion. To minimize pain and discomfort, we will use contoured thigh cuffs that are designed for a better fit and more even pressure distribution. In surgical settings, tourniquet cuffs are typically inflated to 100 mmHg above systolic blood pressure for arterial occlusion. Initially, we followed this standard, but after pilot testing, we reduced the cuff pressure. Using pulse oximetry, we confirmed the loss of distal pulsations as an objective indicator of successful occlusion and found that 80 mmHg above systolic consistently eliminated pulsatile signals while causing less discomfort than 100 mmHg.

Due to the pain and physical location, it is not feasible to blind either the subjects or the investigators to the thigh cuffs. An occlusion lasting a period of three minutes is within the safe inflation time of 1.5 to 2 hours [17].

LBNP is an established model of hypovolemia that has been used since the 1960s. It is considered to entail minimal risk in healthy humans. No serious adverse effects, such as deep venous thrombosis, have been reported [15]. Our research group has extensive experience utilizing LBNP to investigate various clinical scenarios [33,34], having included more than 100 subjects in the last 10 years.

It is important to note that there are differences between traumatic and simulated hemorrhage, as traumatic hemorrhage also involves tissue damage that leads to complex genomic, cellular, tissue and organ alterations [35]. In this present study, the subjects will be exposed to simulated hemorrhage for six minutes in each experimental condition, which is shorter than most clinical hemorrhagic cases. In addition, we will only study circulation in the healthy human brain, whereas the traumatized brain may behave differently.

We will use suprasternal Doppler ultrasound to obtain stroke volume [21]. It has been shown that the systolic velocity profile in the LVOT remains rectangular with little change in velocity from the aortic orifice for 3–4 cm above the aortic valve, even if the aortic diameter changes slightly [21]. Thus, the sampling volume may be positioned in the ascending aorta to minimize noise and improve the quality of the Doppler signal without reducing the accuracy [21]. The ultrasound probe will be positioned in the suprasternal notch, a defined anatomical landmark. This localization will provide a fixed angle of insonation during the experiment [36], which is important as the measured velocity depends on the cosine of this angle. When measuring blood velocity in the MCA using TCD, the same considerations for the angle of insonation apply. It is therefore important not to move the ultrasound probe during the experiment. As the diameter of the MCA cannot be measured, it is assumed to be a constant throughout the experiment [22,37].

For safety reasons, LBNP and thigh occlusion will not be released simultaneously. Thigh occlusion will be relieved 30 seconds after LBNP to prevent excessive hypotension from relieving thigh occlusion before the effects of LBNP have subsided.

In recent years, partial REBOA has gained interest due to its association with lower rates of mortality and organ dysfunction compared to complete REBOA [38]. The technique involves controlled, partial inflation of an intra-aortic balloon catheter. This reduces distal blood flow while maintaining limited perfusion to organs distal to the occlusion site [39,40]. Complete REBOA is associated with a higher risk of complications in patients with hemorrhagic shock [41]. We may use insights from the present study to develop future models of partial occlusion, aiming to replicate the physiological effects of partial REBOA.

In conclusion, this present study aims to combine LBNP and thigh cuff inflation to investigate the systemic and cerebral hemodynamic effects of thigh cuff inflation during LBNP in healthy volunteers.

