### Randomization

The subjects will be randomized in a ratio of 1:1 to begin the test session with one of the two experimental conditions: LBNP alone or LBNP combined with thigh cuff inflation. To ensure an approximately equal number of subjects beginning the test session with either experimental condition, we will use block randomization with blocks of four or eight using the “blockrand” package in R [20]. Allocation will be concealed using sealed, opaque envelopes with sequential allocations, prepared in advance by a person otherwise not involved in the study. This will ensure that group assignment will remain unknown to the enrolling investigator until start of the experiment.

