### Measurements and data processing

Ascending aortic blood velocity will be measured using suprasternal pulsed Doppler ultrasound, with a 2 MHz probe (SD-50; Vingmed Ultrasound, Horten, Norway). Stroke volume will be calculated as the product of the aortic blood velocity-time integral and the left ventricular outflow tract (LVOT) area. The diameter of the LVOT will be measured with echocardiography in the parasternal long-axis (1–5 MHz M5S probe, Vivid E95; GE Vingmed, Horten, Norway) [21], and the area will be calculated assuming a circular LVOT. The heart rate will be calculated from a three-lead ECG (Bio Amp/PowerLab, AD Instruments, Bella Vista, Australia). Cardiac output will be calculated as the product of heart rate and stroke volume.

The arterial blood pressure waveform will be measured continuously and noninvasively using the volume clamp method on the third finger of the left hand (Human NIBP Nano System; Finapres Medical System B.V., Netherlands). End-tidal CO_2_ (ETCO_2_) will be measured with sidestream capnography (Medlab CAP 10; Medlab GmbH, Stutensee, Germany). The photoplethysmography (PPG) waveform from the first toe on the left foot will be obtained using a pulse oximeter (Masimo Radical 7; Masimo Corp, CA, USA).

We will measure MCAV using triplex transcranial Doppler (TCD) ultrasound with a 1–5 MHz M5S probe (Vivid E95). The probe will be positioned over the right anterior temporal window and the middle cerebral artery (MCA) will be identified by its characteristic shape, depth (25–50 mm), and blood flow direction [22]. The sample volume will be placed to obtain a clear Doppler signal with a minimal insonation angle. The probe position and ultrasound machine settings, including the sample volume and angle will not change during both experimental conditions within each subject. The same operator will perform all TCD measurements to ensure reliability and uniformity in data collection. Cerebral tissue oxygen saturation (ScO_2_) will be obtained using near-infrared spectroscopy (Invos 5100C cerebral/somatic oximeter; Somanetics, Troy, MI, USA).

Pain will be registered using a verbal numerical rating scale (VNRS), ranging from 0 (no pain) to 10 (worst imaginable pain). To minimize psychomotor and biofeedback responses during the protocol, subjects will be asked to rate their pain once after completing both conditions. As pain was not a predefined endpoint, we will conduct a post hoc analysis of these data.

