Stroke volume, heart rate, cardiac output, MAP, ETCO_2_ and PPG waveform will be sampled at 1000 Hz using Lab Chart 8.1.28 (ADInstruments, Bella Vista, Australia). MCAV recordings will be exported as AVI-files to Cardiovascular Suite 4.0 (Quipu, Pisa, Italy) for Doppler waveform analysis to calculate the time-averaged maximum velocity. To synchronize the timing of the TCD recordings with the other recorded signals, the recordings will be mirrored directly into Lab Chart 8.1.28 via Digital Visual Interface (DVI) using a video grabber. ScO_2_ data will be exported as.txt-files. Analyses will be performed in R [23] using RStudio [24].

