### Outcomes

The primary outcome is the effect of thigh cuff inflation on stroke volume during LBNP. The secondary outcomes are the effects of thigh cuff inflation on MAP and MCAV during LBNP.

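### The no-blinding statement should be limited to the experimental session: MCAV is read afterwards from exported files, and that step, with any offline cleaning of stroke volume and MAP, can be masked to condition

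*Protocol article*

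**What the plan says.** All the text on blinding is one sentence under Methodological considerations. Citing pain and where the cuffs sit, it states that "it is not feasible to blind either the subjects or the investigators to the thigh cuffs". It is not restricted to the session, and it does not mention whoever processes the recordings.

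Under Outcomes, "The primary outcome is the effect of thigh cuff inflation on stroke volume during LBNP", and "The secondary outcomes are the effects of thigh cuff inflation on MAP and MCAV during LBNP".

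Measurements and data processing describes how these are obtained:

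- **MCAV:** "MCAV recordings will be exported as AVI-files to Cardiovascular Suite 4.0 (Quipu, Pisa, Italy) for Doppler waveform analysis", from which a time-averaged maximum velocity is calculated. This takes place after recording.
- **Stroke volume:** "Stroke volume will be calculated as the product of the aortic blood velocity-time integral and the left ventricular outflow tract (LVOT) area". It is listed with MAP and the toe photoplethysmogram (PPG) among the signals sampled in Lab Chart. Whether a person edits the aortic trace afterwards is not stated.
- **Synchronisation:** the transcranial Doppler picture is mirrored into the same Lab Chart file.

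Under Thigh cuffs, loss of the toe PPG pulse is the check that the cuffs have occluded the arteries. Under Randomization, allocation is concealed in opaque envelopes "prepared in advance by a person otherwise not involved in the study", and this protection lasts until the experiment starts.

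**The concern.** Acquisition and processing are separate steps. During acquisition the operators can see the cuffs, and nothing can be done about that. Processing of a stored Doppler recording may involve choosing usable segments, dropping artefacts or adjusting an envelope. Someone who knows which exposure had cuffs could make those choices differently in the two conditions, without intending to. The condition is also easy to recognise in the Lab Chart file, because the toe pulse disappears when the cuffs inflate.

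At stake is a small systematic difference between conditions in a within-subject comparison of about 20 people. Randomising the order does not protect against it, since the shift would follow the cuff condition and not the period.

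**Working it through.** **1. Do the reasons cover the conclusion?**

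| Step | Do pain and cuff location prevent masking? | What the article documents |
|---|---|---|
| Subject in the chamber | Yes | Neither subjects nor investigators blinded |
| Doppler and pressure acquisition | Yes, operators are present | One operator for all transcranial Doppler; settings unchanged across conditions |
| MCAV waveform analysis from exported files | No | Offline step documented; reader and masking not described |
| Cleaning or beat selection of stroke volume and MAP | No, if done offline | Signals sampled in Lab Chart; an offline step is inferred |

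The statement is justified for the first two rows. It is unsupported for the third, and for the fourth where such a step exists.

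**2. Is masking possible with this set-up?** MCAV files can be given a random code before they are read. In Lab Chart three things would reveal the condition: the toe PPG channel, event marks, and condition labels. All must be hidden, and the link through the mirrored Doppler video must be kept from the reader.

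**3. How sensitive is the test to a processing shift?** The article gives no figure for such bias, so this is illustration only.

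Inputs from Sample size: SD 11 for the percentage reduction in stroke volume at 60 versus 0 mmHg LBNP; a 10% difference; α = 0.05; power 0.90; 16 subjects, 20 enrolled. Assumptions: a two-sided paired t-test, a difference read as 10 percentage points, and a within-subject correlation ρ that the article does not give.

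SD of the within-subject difference: SD_d = 11 × √(2(1 − ρ)).

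*The plan's own figure first.* With ρ = 0.5, SD_d = 11. A paired t-test then needs 15 subjects for 90% power, and 16 subjects give 92.4%. With ρ = 0.40, SD_d = 12.05, 18 are needed and 16 give 87.3%. Power at 16 is exactly 90% when SD_d is about 11.5 (ρ about 0.45). The stated 16 is therefore consistent with SD_d near 11, which makes 11 a reasonable working value. It remains an assumption.

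*Then the shift.* With n = 20 and SD_d = 11, SE = 11/√20 = 2.46 points. With no true effect and a systematic shift b, the test statistic follows a noncentral t distribution with 19 degrees of freedom and noncentrality b/SE; the two-sided critical value is 2.093.

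| Assumed shift b (points) | b/SE | Type I error |
|---|---|---|
| 0.5 | 0.20 | 5.4% |
| 1 | 0.41 | 6.7% |
| 2 | 0.81 | 12.1% |
| 3 | 1.22 | 21.2% |

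For b = 2 the result also depends on SD_d: 18.6% at SD_d = 8 and 8.5% at SD_d = 15.6 (ρ = 0).

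These figures are for stroke volume, where offline reading is inferred. For MCAV, where it is documented, the article gives no SD, so not even an illustration can be made.

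**The case against.** The strongest reply is that the sentence is true of the session, that it says nothing about readers, and that a journal article may leave masked reading, artefact rules and data lock to a fuller document. Silence would then be no error. Much of this stands. A reader might infer that blinding is ruled out altogether, or that an unblinded team processes the traces knowing the condition. The article says neither. What remains is not silence: the article takes a position on investigators, without limit, for reasons that end when the session ends.

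A reader might also infer that the traces behind the primary outcome are read offline by a person. That is documented for MCAV only, and even there the amount of manual input is not given. The article describes no beat selection or envelope tracing. The recommendation for stroke volume and MAP is therefore conditional on such a step existing.

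The article does have safeguards: randomised order, one transcranial Doppler operator, fixed probe position and settings, and a fixed suprasternal angle. These support comparable acquisition but do not mask later processing. Conversely, masked processing cannot remove bias at acquisition, and a large haemodynamic response may partly give the condition away.

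Finally, the type I error figures rest on an invented shift and an assumed SD of the difference. That is correct. They show sensitivity and are not evidence that bias exists.

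**Conclusion.** The point holds in limited form. The infeasibility of blinding is justified for the session but is stated without that limit. MCAV processing takes place afterwards on exported files and could be masked; so could any offline selection or artefact removal for stroke volume and MAP. The plan as written describes no such masking and so leaves an avoidable route to processing bias.

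The size of any bias cannot be obtained from the documents. In the illustration (n = 20, SD of the difference 11), shifts of 0.5 to 3 points move the type I error from 5% to between about 5% and 21%; a single figure such as 12% should not be quoted as the expected effect. Sample size and study procedures are unaffected. This is an inexpensive improvement of low to moderate severity, and it can still be made on stored recordings.

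**What to change.** 1. Limit the sentence under Methodological considerations to the experimental session.
2. Add to Measurements and data processing that MCAV files are given a random code by a script before waveform analysis.
3. State whether stroke volume and MAP undergo any offline selection or artefact removal. If they do, process them under the same coding, with condition labels, event marks and the toe PPG channel hidden.
4. Lock the processed MCAV, stroke volume and MAP data before the condition is merged.
5. Acknowledge that acquisition stays unmasked and that the response itself may partly reveal the condition.

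The cost is a modest amount of recoding work, since Lab Chart channels and marks must be hidden as well as files renamed, and a short delay before unmasking. No additional reader, procedure, subject or burden on subjects is needed.

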### Trial status

Data collection began in April 2024 and is expected to be completed in February 2025. The results will be submitted for publication in a peer-reviewed international journal and presented at scientific conferences.
